## Protocol

### Objectives

The Primary Objective of the
**I**nterleukin-2
**T**herapy of
**A**utoimmunity in
**D**iabetes (ITAD) trial is to assess the effects of ultra-low dose aldesleukin administration on endogenous β-cell function, as measured by weekly assessments of fasting and post-prandial C-peptide from DBS in children and adolescents with newly diagnosed T1D.

The Secondary Objectives are: 1) To assess the efficacy of regular dosing of aldesleukin in increasing Treg levels; 2) To confirm the clinical safety and tolerability of ultra-low dose aldesleukin; 3) To assess changes in the immune system indicating benefit or potential risk for future gains/loss in β-cell function and immune function; 4) To assess treatment effect on glycaemic control.

Table 1 reports the trial objectives and related outcome measures.

**Table 1. T1:** Study objectives and outcomes.

Objectives	Outcome Measures	Timepoint(s) of evaluation of this outcome measure
**Primary Objective** To assess the effects of ultra-low dose aldesleukin administration on endogenous beta-cell function as measured by frequent home dried blood spot (DBS) fasting and post-prandial C-peptide in children and adolescents with newly-diagnosed type 1 diabetes (T1D).	Differences in slopes of dried blood spot (DBS) C-peptide over the 6 month-treatment period between the active and placebo groups.	Weekly DBS C-peptide collected during the 6-month treatment period, and then monthly during the 6 months of follow-up
**Secondary Objectives** 1) To assess the efficacy of regular dosing of aldesleukin in increasing T-regulatory (Treg) levels	1) Change in Treg, Teff and NK56 ^bright^ cell frequencies from baseline	1) At baseline and then 1, 2, 3, 6 and 12 months from the beginning of treatment
2)To confirm the clinical safety and tolerability of ultra-low dose aldesleukin	2) Safety will be assessed at each visit by: • Physical examination, including assessment of the most commonly reported reactions to low- or high-dose aldesleukin, namely influenza-like syndrome, skin reaction, diarrhoea, nausea; vital signs (temperature, blood pressure, heart rate); weight, abnormal laboratory parameters (liver, kidney function, full blood count); reporting of adverse events.	2) At screening, baseline and then 1, 2, 3, 6 and 12 months from the beginning of treatment

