3) To assess changes in the immune system indicating benefit or potential risk for future gains/loss in beta-cell function and immune function.	3) Changes in the absolute numbers of T, B and NK cells. A whole blood 6-color BD TBNK Multitest™ assay using BD Trucount Tubes according to the manufacturers’ instructions (BD Biosciences) will be run to determine the relative and absolute concentration of lymphocyte subpopulations, including T, B and NK cells.	3) At baseline and then, 1, 2, 3, 6 and 12 months from the beginning of treatment
4) To assess treatment effect on glycaemic control	4) Change in HbA1c and daily insulin requirements during the trial period.	4) HbA1c - At baseline and then 3, 6 and 12 months Insulin dose data -Baseline and then 1, 2, 3, 6 and 12 months

**DBS: **dried blood spot;
**PBMC:** peripheral blood mononuclear cell;
**TBNK FACS:** T-cell, B-cell and NK cell Fluorescence activated cell sorting;
**Teff:** T effector cells;
**Treg:** T regulatory cells
**T1D: **type 1 diabetes

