### Collection of home dried blood spots

Instruction, both oral and written (provided as extended data
^36^), will be given to participants/parents at the baseline visit about collection of DBS samples at home between hospital visits, and in the first week of treatment, the research nurse will provide further instruction on the DBS collection and the DBS collection will be supervised by them, where possible. Copies of instructions will be provided in the investigator site file.

DBS sampling will be done once a week (+/- 2 days), (before and after a liquid meal or standardised breakfast) from baseline until treatment end at 6 months, and then monthly up to 12 months, for the measurement of C-peptide. If the DBS sample is taken on a treatment day, then the sample must be taken before treatment is given.

DBS samples and blood glucose measurements will be taken fasting immediately before a standardised meal (the first meal of the day), consisting in the Ensure Plus drink, and at 60 minutes from the start of consuming the drink, by finger prick in the home setting. If blood glucose is not between 4 and 11.1 mmol/l, they should take the DBS samples on another day. Participants who are not able to tolerate Ensure Plus will be advised to eat a standardized breakfast with a defined content of carbohydrates, proteins and lipids, which will need to be the same for all DBS collections during the study. Details are provided in the Investigator Site File.

Participants will be asked to withhold their pre-breakfast insulin until after the post-prandial DBS samples have been taken so as not to interfere with the C-peptide result. Following the 60-minute DBS sample, the patient will give a correction dose either via injection or pump, according to the patient’s own insulin sensitivity factor.

The completed DBS card will then need to be air dried for 24 hours before being posted to the laboratory in the pre-paid envelope provided.

DBS collection can be facilitated, when possible, by the research nurses during their twice-weekly home visits to dispense aldesleukin/placebo. Reminders to patients to do the DBS will be provided by the research nurses at their visits. Reminders post-treatment will be given by site staff at participating study sites via a text message or telephone call.

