### Early discontinuation/withdrawal of participants

During the course of the trial participants or their parents/guardians may choose to withdraw early from the trial treatment at any time. This may happen for a number of reasons, including but not limited to: 1) The occurrence of what the participant perceives as an intolerable AE; 2) Inability to comply with trial procedures; 3) Participant decision. Participants may choose to stop treatment but may remain on study follow-up. Participants may also withdraw their consent, meaning that they wish to withdraw from the study completely. Under these circumstances, the site needs to document all relevant discussions in the patient notes and notify the Trial Office, which will allow the office to mark all future electronic case report forms (CRFs) as not applicable.

Under these conditions, investigators are still responsible to follow up any serious adverse event (SAEs) until resolution. Data collected up to the time of consent withdrawal will be used in the analysis. No further data or samples would be collected after withdrawal.

In addition, the Investigator may discontinue a participant from the trial treatment at any time for any reason including, but not limited to: 1) Pregnancy; 2) Ineligibility (either arising during the trial or retrospectively having been overlooked at screening); 3) Significant protocol deviation; 4) Significant non-compliance with treatment regimen or trial requirements; 5) An AE which requires discontinuation of the trial medication or results in inability to continue to comply with trial procedures; 6) Disease progression which requires discontinuation of the trial medication or results in inability to continue to comply with trial procedures

The type of withdrawal and reason for withdrawal will be recorded in the CRF.

If the participant is withdrawn due to an AE, the Investigator will arrange for follow-up visits or telephone calls until the adverse event has resolved or stabilised.

If a participant is withdrawn from treatment due to pregnancy, the pregnancy will be followed up to outcome.

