Any parents or guardian of the participant or the participant requesting to withdraw from intervention will be asked if they want to continue to attend study visits and to complete all study assessments. If they agree then they will be put on to the post-treatment follow-up schedule of monthly DBS and a final visit after 6 months of follow up. During this time all participants will continue to receive the same level of supervision as received by other study patients.

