## Statistics

### Description of statistical methods

Full details of the statistical analysis will be detailed in a separate statistical analysis plan (SAP) which will be drafted early in the trial and finalized prior to the primary analysis data lock.

Descriptive statistics will be used to describe the demographics between the treatment groups. The primary outcome is change in DBS C-peptide (slopes) during the 6-month treatment period. This will be analysed using Analysis of Covariance (ANCOVA) with adjustment for stratification factors (site, age group) and baseline C-peptide values. Between group differences with corresponding 95% confidence intervals will be reported. If not normally distributed, non-parametric methods will be used with no adjustment (for example the Mann-Whitney Test or Kruskal-Wallis test).

Standard statistical tests will be used to compare the actively treated group with the placebo group (t test, Mann Whitney U-test, analysis of covariance, chi square test), with P values below 0.05 indicating significance.

The incidences of adverse events will be reported and, where appropriate, the two groups will be compared with the use of a logistic regression model.

Analyses will be undertaken on an intent to treat population (all patients analysed as randomised) with sensitivity analyses undertaken to explore deviations from the protocol and compliance with treatment.

An interim analysis based on safety measures is planned for the age-based step-down approach. The plan is to expose to treatment firstly six participants in the age group 12–18 years for a minimum of one month. If after review of the unblinded external safety data and satisfactory safety is established, recruitment will be extended to the younger age group, 6–11 years.

Stata (StataCorp LP) or other appropriate validated statistical software will be used for analysis.

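### Families who stop injections but agree to all assessments are moved to a reduced schedule, so month-3 and month-6 secondary outcomes go uncollected and the primary slope is thinned

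*Protocol article*

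**What the plan says.** Under Early discontinuation/withdrawal of participants, a participant, parent or guardian who asks to withdraw from the intervention "will be asked if they want to continue to attend study visits and to complete all study assessments". For those who agree, "they will be put on to the post-treatment follow-up schedule of monthly DBS and a final visit after 6 months of follow up". The section End of treatment and long-term follow-up assessments shows what that schedule is: monthly home DBS, and one formal assessment at the end of the six months.

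Table 1 defines the primary outcome as "Differences in slopes of dried blood spot (DBS) C-peptide over the 6 month-treatment period between the active and placebo groups", with the collection time given as "Weekly DBS C-peptide collected during the 6-month treatment period, and then monthly during the 6 months of follow-up". The home-sampling section agrees: "DBS sampling will be done once a week (+/- 2 days" from baseline to month 6. Table 1 counts the secondary time points from treatment start. Treg/Teff/NK, TBNK and insulin dose are due at baseline and months 1, 2, 3, 6 and 12. For HbA1c it says "HbA1c - At baseline and then 3, 6 and 12 months".

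On the analysis population, the statistical methods section says: "Analyses will be undertaken on an intent to treat population (all patients analysed as randomised". Dose delays and missed doses likewise promises intention to treat for children with treatment breaks or dropout, with sensitivity analyses. No section keeps weekly DBS, or the remaining visits at months 1, 2, 3 and 6, for a child who has stopped injections at the family's request.

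**The concern.** The two sentences of the withdrawal paragraph do not fit together. A family that agrees to everything is then assigned less, by rule. The reduced schedule appears to run from the stop rather than from treatment start, so the values that Table 1 calls for at fixed calendar months are not collected in those children.

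An intention-to-treat comparison at month 3 or month 6 needs the same measurement in children who stopped and children who continued. Here the missing values belong to children who stopped, although they were willing to attend. The family's listed reasons for stopping include an adverse event perceived as intolerable, so the missingness is plausibly related to tolerability, and it could differ by arm. This is a rule about data collection, so the statistical analysis plan cannot repair it afterwards.

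**Working it through.** **Inputs from the protocol article.** Weekly DBS from baseline to month 6, taken as weeks 0–26 (27 time points). Visits at months 1, 2, 3, 6 and 12, each within 7 days (Table 3). Slope difference 0.53, SD 0.523, 24 active and 12 placebo, increased by 25% to 45 (Power calculation).

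**Assumed, because the documents do not give them.** A two-sided 5% test; a month of 4.345 weeks; the stopping week; the share of children who stop; and the share *r* of slope variance at weekly sampling that is measurement error. The reduced schedule is taken to start at the stop, which is the natural reading.

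**1. The plan's own figure.** The noncentrality is 0.53 / (0.523 × √(1/24 + 1/12)) = 2.87 on 34 df, giving power of 79.5% (81.8% by normal approximation). The stated 36 and 80% reproduce. Also 36 × 1.25 = 45 = 36/(1 − 0.20). With all 45 contributing (30:15), power is 87.9%.

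**2. Visits lost.** The final visit falls at stop + 6 months.

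| Stop (month) | Scheduled visits dropped | Final visit (month) |
|---|---|---|
| 1.5 | 2, 3, 6 | 7.5 |
| 2.5 | 3, 6 | 8.5 |
| 4 | 6 | 10 |

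The month-12 visit is displaced in each case. Only a stop within about the first week puts the final visit inside the 7-day window around month 6.

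**3. One child's primary slope.** The measurement-error variance of a least-squares slope is σ²/Sxx, with Sxx = Σ(t − t̄)². Full weekly sampling gives Sxx = 1638.

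| Stop (week) | Readings, weeks 0–26 | Sxx | Variance ratio *k* |
|---|---|---|---|
| 4 | 5 + 5 = 10 | 764 | 1638/764 = 2.14 |
| 8 | 9 + 4 = 13 | 766 | 1638/766 = 2.14 |
| 13 | 14 + 3 = 17 | 835 | 1638/835 = 1.96 |

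For a week-13 stop, 14 of the 17 readings precede the stop, so the slope leans towards the on-treatment period.

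**4. Trial level.** If 25% of children stop, the average slope variance is multiplied by 1 + 0.25 × *r* × (*k* − 1). With *k* = 2.14 this is 1.029 at *r* = 0.1 and 1.143 at *r* = 0.5. Power at N=45 goes from 87.9% to 87.0% and 83.4% respectively; with *k* = 1.96 it goes to 87.2% and 84.1%. At N=36 the 79.5% becomes about 74–79%. This counts lost precision only, not bias.

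**5. Month-6 secondary outcomes.** If 9 of 45 children (6 active, 3 placebo) lacked the value, the standard error ratio would be √[(1/24 + 1/12)/(1/30 + 1/15)] = √(0.125/0.100) = 1.118, a rise of 12%.

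**The case against.** Several stronger readings are tempting, and the documents do not support them.

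- *The primary outcome is lost.* It is not. Six months of monthly DBS after any stop reaches month 6, so a child who keeps to that schedule still has a slope over the whole window. The doubling applies to the measurement-error part of one child's slope. At N=45 the illustrated power stays above the planned 80%.
- *The loss is driven by worsening disease.* Disease progression appears only among the investigator's reasons for discontinuation, and the reduced schedule is written for withdrawal requested by the family. The supported link is to tolerability. The article states no assessment schedule after an investigator's decision.
- *The protocol expects nine stoppers.* The 25% increase covers dropouts and extended periods off treatment together. Children who withdraw consent give no further data under any schedule, and treatment breaks do not trigger the reduced one. Nine is therefore an upper illustration.
- *The secondary comparisons become purely on-treatment comparisons.* Children with skipped doses or breaks remain on schedule, and a stop after month 3 keeps the month-3 values.

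Two further points in the plan's favour count in part. It provides for sensitivity analyses and, if appropriate, multiple imputation, but neither recovers samples never taken. An end-of-trial assessment is required when a child stops for an adverse event, but its time point is not given.

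The best remaining defence is retention. Weekly fasting samples are a burden, nurse visits for injections would have ended, and a lighter schedule may keep families who would otherwise leave altogether. That stands as a reason to offer a reduced schedule, but not as a reason to impose it on families who accept the full one.

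**Conclusion.** The point holds as an internal conflict with a limited, avoidable cost. The withdrawal paragraph contradicts itself and does not fit Table 1 or the intention-to-treat analysis. Its main effect is that month-6 secondary values, month-3 values for earlier stops, and the month-12 visit are missing or displaced by rule in children whose families agreed to stay. Stops in the first two months also lose visits at months 1 or 2. A very early stop is the exception for month 6.

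The effect on the primary analysis is modest: about 1 to 5 points of power at N=45, assuming 25% stopping at weeks 4 to 13 and a 10–50% measurement-error share. The 12% rise in standard error for month-6 outcomes rests on an assumed nine children. Bias from unequal stopping between arms is possible, but cannot be sized from the documents. This is a worthwhile and inexpensive correction, and it does not invalidate the primary analysis.

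**What to change.** Reconcile the withdrawal paragraph with Table 1 and the intention-to-treat analysis. State that a child who stops injections, by family request or investigator decision, but stays in the study keeps the original assessment calendar counted from treatment start. That means weekly fasting and post-prandial DBS to month 6; the remaining Visits 3 to 6 with their HbA1c, insulin-dose, Treg/Teff/NK and TBNK assessments; then monthly DBS to month 12 and the month-12 visit. Offer the reduced schedule only if the family declines the full one, and record that choice. The change concerns assessments only, not treatment.

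The cost is one protocol paragraph, some extra DBS cards, the visits already planned, and text or telephone reminders of the kind already foreseen after treatment. The downside is sampling and visit burden on families who have stopped treatment, which the recorded fallback limits.

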## Intervention

### Legal status of the investigational medical product (IMP)/placebo

Aldesleukin (Clinigen; generic name aldesleukin; trade name, Proleukin) has been available as an approved drug since 1992. The main clinical indication for aldesleukin is treatment of adults (≥18 years of age) with metastatic renal cell carcinoma and metastatic malignant melanoma. In this trial, aldesleukin is being used outside of its licensed indication and being carried out under a Clinical Trial Authorisation. The drug is therefore only to be used by the named Investigators, for the patients specified in this protocol, and within the trial.

The components of the placebo, Water for Injections Ph. Eur., and glucose 5% are both licensed products. Glucose 5% is licensed as a solution for infusion and the water as a solvent for parenteral use. Both are being used within the terms of their licenses.

### Storage and supply of aldesleukin/placebo

The pharmacy at each participating site will prepare and dispense aldesleukin and placebo for this study following instructions received from the Trial Office, and upon receipt of a suitably signed trial-specific prescription.

On receipt of a valid trial prescription containing the subject trial number, date and visit number, the trial pharmacist will first check the treatment allocation through the RRAMP system or refer to the email sent to them upon randomisation to ascertain whether patient is to receive active treatment or placebo.

For each individual participant, a single concentration of the aldesleukin or placebo will be aseptically prepared for administration in individual insulin syringes for each dose.

Each vial of aldesleukin powder for solution for injection contains 22 × 10
^6^ IU aldesleukin. Aldesleukin contains less than 23 mg sodium per 1 ml and can be considered as 'sodium-free'. The powder is sterile, white and lyophilized. For all injections, aldesleukin is first reconstituted as per aldesleukin summary of product characteristics (SmPC) with water for injection. Solutions are then further diluted to the required concentration in 5% glucose as per the Ceplene SmPC (Noventia Pharma SRL). Vials need to be stored at 2°C to 8°C (in a refrigerator) and protected from light.

Placebo will be prepared with sterile diluent used for the aldesleukin preparation and 5% glucose in appropriately labelled syringes (identical to that used for the diluted active drug) and will be supplied by the study pharmacy to the study nurse/doctor.

Previous data supports stability and sterility of reconstituted diluted IL-2 preparations (reconstituted with as per the aldesleukin SmPC and further diluted with glucose 5% as per the Ceplene SmPC) for up to 14 days at 2–8°C when syringes are prepared by qualified health-care professionals under aseptic conditions and for up to 30 days at room temperature
^37^. However, following Section 10 (Medicines Act), for this study the aseptically prepared product will have an expiry date of 7 days after preparation when stored at 2–8°C. Therefore, syringes containing aldesleukin/placebo will be delivered twice-weekly by the trial research nurses to study participants and the drug either administered by the nurse or self-administered by the participant/carers under the nurse’s supervision.

Syringes will be labelled with trial-specific labelling provided by the trials office that will enable blinding to be maintained. Records of trial treatment allocations will be kept in pharmacy, Drug Dispensing and Accountability Logs will be provided.

All doses that are not used will be returned to the pharmacy at the participating site and a record of their disposal will be made.

### Accountability of the trial treatment

The pharmacies will dispense the drugs to the research nurses (or other members of the study team approved by the Principal investigator), who will deliver the study drugs to the participants. The nurses will be asked by the pharmacists to sign when they collect the IMP and to request the participants’ signature when they deliver the IMP, as well as when patients return the IMP. The nurses will also be asked to sign when they return any unused IMP.

### Compliance with trial treatment

Subject attendance and compliance will be recorded for all visits. At each visit, any unused drug vials will be returned.

### Dose delays and missed doses

Doses should not be delayed, but rather should be skipped. Treatment breaks will be considered based on participants’ individual needs e.g. a planned holiday, by discussion with the Trial Office.

In the circumstances of participants with treatment breaks and those who drop out of the trial an intention-to-treat analysis with secondary sensitivity analyses will be conducted taking these into account, and the sample size accounts for these circumstances.

